### Multiple testing

No formal adjustment will be made for multiple testing. However, the following measures to avoid problems with over-interpretation will be taken: (a) formal statistical comparisons will not be made for outcomes with low event rates, and (b) only pre-specified subgroup analyses will be performed and a significance level of 5% will be used for the tests for interaction for subgroup analyses despite being low powered tests. Consideration will be taken in the interpretation of results to reflect the number of statistical tests performed and the consistency, magnitude and direction of treatment estimates for different outcomes.

### Missing data

All missing data will be described by treatment group. If the amount of missing data differs substantially between groups, potential reasons will be explored. The following approach will be used to handle missing data in analysis models.

#### Missing predictor data

By design, there will be no missing data for any of the randomization factors. All other potential predictors are preoperative measurements of continuous longitudinal outcomes; by using the joint modelling approach described, missing values for such data are considered in the context of missing longitudinal data (see next).

Approaches for dealing with missing continuous outcome data measured at one time point are described in Table 4.

**Table 4 Tab4:** **Missing continuous outcome data measured at one time point**

**Amount of missing data**	**Rule**
Less than 5%	Complete case analysis will be performed, that is excluding cases with missing data.
Between 5% and 15%	Marginal mean imputation will be performed, that is imputing the overall median or mean.
Between 15% and 25%	Conditional mean imputation methods will be used. This involves predicting the outcome from a regression model from (linearly related) covariates.
Above 25%	Multiple imputation will be considered. A general imputation model that uses an iterative procedure to generate imputed values will be used to generate multiple complete data sets. The model of interest will be fitted to each of the complete data sets and effect estimates combined using Rubin’s rules.

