#### Continuous outcomes

These will be summarized by the mean and standard deviation (or median and interquartile range if data are skewed) in each treatment group and compared using linear regression. For untransformed data, treatment comparisons will be presented as adjusted differences in means with 95% confidence intervals, and for logarithmically transformed data as adjusted ratios of geometric means with 95% confidence intervals. If a logarithmic transformation is not satisfactory other analysis or presentation methods will be sought.

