### Adjustment in models

The intention is to adjust all models for factors included in the cohort minimization: operation type (four different types) as a fixed effect and centre (17 different centres) as a random effect (or a shared frailty term in time-to-event models). Occasionally, the operation type might differ between the study database and the randomization system because it has been entered incorrectly into the randomization system. In this case, the value from the study database will be used, as the operation type recorded on the database will have been confirmed to be correct in such instances. For all treatment comparisons, the liberal group will be the reference group.

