## Discussion

We prospectively present the approach that will be taken in the analysis of the TITRe2 randomized controlled trial. Publishing the statistical analysis plan will increase transparency and promote deeper understanding of the methods used within the study. This transparency should reduce the risk of reporting data- or method-driven results.

During the peer review of this paper, it was pointed out that the marginal mean imputation method is not advisable for any level of missing data because it is likely to underestimate the variance of the treatment effect. We have not revised Table 4 because the analysis plan has since been executed and, in the event, this method of imputation was not implemented. However, we acknowledge that the method is inappropriate. We have revised the analysis plan template in our trials unit so that this method will not be proposed in further statistical analysis plans.

In preparing the statistical analysis plan, we have very deliberately sought to include our plans for additional, or secondary, analyses using trial data that are not directly related to the trial objectives. Doing this has compelled us to plan and consider the analysis approach and implications for the whole study collectively rather than in a fragmented manner. We believe that this has helped us formulate these plans more precisely and allows us to document that the plans were set out in advance of any data exploration. We recommend this approach to other researchers; otherwise, because the researchers are the ones performing the primary analyses, it can be difficult for them to substantiate a claim of pre-specification for a secondary analysis and to avoid criticisms of selective reporting in ways that have recently been identified in reports of the primary results of randomized controlled trials [20].

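### Table 4's conditional-mean rule for 15–25% missing continuous outcomes gives either intervals that are too narrow or a diluted effect, and the Discussion's correction does not reach it

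*SAP article*

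**What the plan says.** Table 4 of the SAP article sets four rules by the amount missing. Below 5%, cases with missing values are dropped. From 5% to 15%: "Marginal mean imputation will be performed, that is imputing the overall median or mean". From 15% to 25%: "Conditional mean imputation methods will be used. This involves predicting the outcome from a regression model from (linearly related) covariates". Above 25%, multiple imputation is to be considered, and for that row only the table says how the imputation uncertainty is carried: "The model of interest will be fitted to each of the complete data sets and effect estimates combined using Rubin’s rules".

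Under Continuous outcomes, the data are summarized "in each treatment group and compared using linear regression", with 95% confidence intervals. Under Adjustment in models, the covariates are "operation type (four different types) as a fixed effect and centre (17 different centres) as a random effect".

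The Discussion reports a peer-review comment that the "marginal mean imputation method is not advisable for any level of missing data because it is likely to underestimate the variance". The authors accept this, say that this method was not used in the event, leave Table 4 unrevised, and remove the method from their unit's template. They do not mention the conditional-mean row.

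**The concern.** Conditional-mean imputation puts a value exactly on the regression line for every missing patient. Nothing in Table 4 adds a residual draw, a bootstrap or any other correction. The regression that follows treats these values as observed, so it counts too many patients and sees too little scatter.

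The table also does not say whether allocation is among the predicting covariates. If it is, the interval is too narrow. If it is not, imputed patients in both arms are given values that ignore the treatment difference, and the estimate is pulled toward zero. The reported estimate and interval for an affected outcome would be wrong either way, and in the first case the P value too.

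**Working it through.** Table 4 states no standard error, coverage or error rate, so it has no figure to reproduce. The article's one design figure, 1,468 patients for 17% versus 11%, does reproduce (734 per arm with continuity correction, 90% power, two-sided 5%), but it has no bearing here.

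**Inputs.** From the article: m = 0.15 to 0.25 (Table 4); linear regression with 95% intervals (Continuous outcomes); N = 2,000 and 1:1 allocation (Methods and Design). Assumed: values missing completely at random; for the simulation, one covariate with R² = 0.30 and a true difference of 0 or 0.145 SD. The article gives neither of the last two values.

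**Case A: allocation included, imputation model equal to the analysis model.** The estimate equals the complete-case estimate. With residual SD σ:

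- True SE = 2σ/√(N(1−m)).
- Imputed rows have zero residual, so the residual variance falls to (1−m)σ² while all N rows are counted. Naive SE = 2σ√(1−m)/√N.
- Ratio, naive to true = √(1−m) × √(1−m) = 1−m.
- Coverage = 2Φ(1.96(1−m)) − 1; type I error is the complement.

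| m | SE ratio | Coverage | Type I error | Simulated type I error |
|---|---|---|---|---|
| 15% | 0.85 | 90.4% | 9.6% | 10.2% |
| 20% | 0.80 | 88.3% | 11.7% | 10.7% |
| 25% | 0.75 | 85.8% | 14.2% | 14.8% |

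The simulation used 3,000 runs per cell. At m = 20%, σ = √0.70 = 0.837 gives a true SE of 2 × 0.837/√1,600 = 0.0418 and a naive SE of 0.80 × 0.0418 = 0.0335. These equal the average SEs in the simulated complete-case and imputed analyses.

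**Case B: allocation included, plus a predictor that is not in the analysis model.** Table 4 speaks only of linearly related covariates, so this is possible. Take R² = 0.2 for that predictor (assumed) and a total variance of 1:

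- Naive variance ∝ 1 − m + mR²; true variance ∝ (1−R²)/(1−m) + R².
- m = 15%: 0.880/1.141 = 0.771, SE ratio 0.878, type I error 8.5%.
- m = 20%: 0.840/1.200 = 0.700, SE ratio 0.837, type I error 10.1%.
- m = 25%: 0.800/1.267 = 0.632, SE ratio 0.795, type I error 11.9%.

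**Case C: allocation omitted.** Only the observed fraction carries the difference, so the estimate is about (1−m)δ. For δ = 0.145 this is 0.123, 0.116 and 0.109; the simulation gave 0.124, 0.115 and 0.109. Coverage of the true difference was 90%, 86% and 80%. The naive SE and the actual spread of the estimate shrink by the same factor as the estimate, so the test statistic is essentially that of the complete-case analysis. Simulated type I error was 4.8%, 5.1% and 4.8%.

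**Comparison.** Adjusted complete-case regression in the same simulation gave coverage of 94.8–95.7% and type I error of 4.3–4.8%, with no dilution.

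**The case against.** The strongest reply concerns reach. Table 4 applies to continuous outcomes measured once, and Table 2 lists four: red cell units, fresh frozen plasma, cryoprecipitate and platelets. All are secondary. The red cell and blood-component outcome is defined over the hospital stay, so it does not depend on the follow-up questionnaire, and nothing in the article suggests that 15–25% would be missing. This stands, and it limits the severity. It does not make the rule sound if it is triggered.

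A reader might infer that the whole 5–25% range is a live defect. The article does not support that: the Discussion calls the marginal-mean method inappropriate and says it was not used. Its stated reason, that "it is likely to underestimate the variance of the treatment effect", omits the dilution caused by imputing one overall mean in both arms, but a rule that has been withdrawn need not be argued again.

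A reader might also infer that P values are wrong whichever imputation model is used. They are not. In Case C the test keeps its level, and only the estimate and interval are distorted. The inflated type I error depends on allocation being in the imputation model, which the plan leaves open.

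Nor does the article show that any reported result was affected. It says the plan has been executed, but not how much was missing or whether the conditional-mean row was used.

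Finally, it can be argued that multiple imputation is not needed. That is right: complete-case regression was valid in the simulation, and when only the outcome is missing and the imputation covariates are already in the analysis model, multiple imputation adds essentially nothing.

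**Conclusion.** The point holds for the 15–25% row. As written, that row produces intervals covering about 90% to 86% with type I error of 9.6–14.2% (Case A), type I error of about 8.5–12% (Case B, with R² = 0.2 assumed), or an estimate and interval shrunk by 15–25% with a valid test (Case C). The size rests on values missing completely at random. The (1−m) factors in Cases A and C do not depend on R²; the Case B figures do.

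The Discussion leaves the row in place, although its variance objection applies equally to Cases A and B. The consequence is confined to the four transfusion outcomes, and to the event that 15–25% of one is missing. A reader might take this as a threat to the trial's main finding, but the article rules that out: the primary outcome is binary with no formal imputation, and EQ5D is handled by the mixed model. Severity is minor to moderate.

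**What to change.** Delete the conditional-mean row of Table 4. At 15–25% missing, use one of two methods, named in advance:

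- Adjusted complete-case linear regression. This also agrees with the Patient population section, which leaves patients with missing outcome data out of the analysis.
- Multiple imputation with allocation, operation type, centre and any predictors of missingness in the imputation model, combined by Rubin's rules.

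Replace the already conceded 5–15% row in the same way. Extend the Discussion's correction to conditional-mean imputation, and state whether that row was used for any outcome. Because the plan has been executed, this statement tells the reader whether any reported interval needs recalculating.

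The cost is wording, plus re-analysis of any outcome for which the row was used. In Case A the intervals become about 18% wider at 15% missing (1/0.85 = 1.18) and 33% wider at 25% missing (1/0.75 = 1.33), which is their correct width.

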#### Missing longitudinal continuous outcome data

Preoperative values will be modelled jointly with those measured postoperatively, as described, thereby allowing all cases with at least one observation to be included. If appropriate (the level of missingness is >20%) then any variables that are predictive of missingness will be identified, and if there is reason to suggest that an assumption of missing at random given these variables is reasonable (this is especially likely if the variable was measured pre-operatively) then such variables will be adjusted for in the models of interest. These models can be shown to provide unbiased estimates of the treatment effect; moreover, multiple imputation approaches would not be expected to recover any additional information [12].

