**Table 2 Tab2:** **Classification of primary and secondary outcomes**

**Category**	**Outcomes**
Binary outcome measures	• Primary outcome measure: proportion of patients experiencing an infectious or ischaemic event
	The following secondary outcome measures:
	• Proportion of patients experiencing an infectious event
	• Proportion of patients experiencing an ischaemic event
	• Use of activated factor seven
	• Use of Human Blood Coagulation Factor IX
	• Significant pulmonary morbidity
Continuous outcome measures	The following secondary outcome measures:
	• Units of RBCs transfused
	• Fresh frozen plasma transfusions
	• Cryoprecipitate transfusions
	• Platelet transfusions
Time-to-event outcome measures	The following secondary outcome measures:
	• Time from randomization to first occurrence of the primary outcome measure (secondary analysis of the primary outcome measure)
	• Duration of post-randomization stay in intensive care or high dependency unit
	• Duration of post-randomization hospital stay
	• Time from randomization to death from any cause
Continuous longitudinal outcome measures	The following secondary outcome measures:
	• EQ5D single summary index score
	• EQ5D visual analogue scale score

General presentation and analysis techniques for each type of outcome are described next.

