#### Continuous longitudinal outcomes

These will be compared using a linear mixed-effects methodology with the treatment group and study design variables fitted as fixed effects, and patient terms as random effects. Separate parameter estimates will be incorporated into models for: (a) the mean baseline response across both treatment groups and (b) each post-randomization time point for each treatment. This approach of ‘jointly’ modelling the baseline and post-intervention measurements avoids the necessity of either excluding cases with missing baseline measures or imputing missing baseline values. If the time by treatment interaction (post-intervention) is not statistically significant at the 10% level, an overall treatment effect will be reported. If the interaction is statistically significant, the changes in treatment effect with time will be described. Different variance/covariance structures will be explored (compound symmetry, first-order auto-regressive, Toeplitz and unstructured), and the structure that provides the best fit using the likelihood ratio test (or Akaike information criterion if compared models are not nested) will be used. Treatment comparisons will be presented as adjusted differences in means with 95% confidence intervals.

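### The EQ5D missing-data rule lets variables affected by allocation into the treatment model, where the claim of unbiased treatment estimates no longer holds

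*SAP article*

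**What the plan says.** Table 2 classes two secondary outcomes as continuous longitudinal: the "EQ5D single summary index score" and the EQ5D visual analogue scale score. Under Continuous longitudinal outcomes they are compared by a "linear mixed-effects methodology with the treatment group and study design variables fitted as fixed effects", with baseline and follow-up values modelled jointly.

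The section on missing longitudinal data then adds a conditional rule:

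- Trigger: "If appropriate (the level of missingness is >20%) then any variables that are predictive of missingness will be identified".
- Second condition: "if there is reason to suggest that an assumption of missing at random given these variables is reasonable".
- Remark on timing: "this is especially likely if the variable was measured pre-operatively".
- Action: "then such variables will be adjusted for in the models of interest".
- Justification: "These models can be shown to provide unbiased estimates of the treatment effect", and "multiple imputation approaches would not be expected to recover any additional information".

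**The concern.** The rule selects covariates by whether they predict missingness and whether missing at random is plausible given them. Neither test asks whether allocation could have changed the variable. The remark on timing offers pre-operative measurement as a favourable case and sets no limit.

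The trial records several post-randomization variables that could plausibly predict an unreturned questionnaire: infectious and ischaemic events, pulmonary morbidity, length of stay and units transfused. These are trial outcomes. The sample size rests on the hypothesis that allocation changes the event rate, and the allocated threshold acts directly on transfusion.

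Putting such a variable in the outcome model changes the question. The treatment coefficient becomes a contrast between arms at equal values of, say, complications, when the stated objective is to compare the two strategies. The result would still be reported as an unbiased treatment effect.

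**Working it through.** **Figures available.** The plan gives no EQ5D effect, SD, missingness rate or predictor of missingness, so there is no plan figure to reproduce on this point. The sample size of 1,468 concerns the primary outcome and plays no part. From the plan come 1:1 allocation, a target of 2,000 and the 20% trigger. All other inputs below are assumptions.

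**Algebra.** Let T be allocation, M a post-randomization variable and Y the follow-up score:

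- M = m·T + noise (SD 1)
- Y = d·T + b·M + noise
- total effect of T on Y = d + b·m

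Let missingness depend on M only, so that missing at random given M holds exactly. Regressing observed Y on T and M recovers d. The gap from the total effect is b·m, the part that runs through M. Missing at random does nothing to close that gap, because the gap arises from conditioning on M and would be present with complete data.

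**Simulation.** N = 2,000, 1,000 replicates, one follow-up. Slope b = −0.5; SD of Y given T about 1. Probability missing = 1/(1 + exp(1.35 − M)), which puts missingness above the 20% trigger. The total effect is 0.20 SD in every row:

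- full mediation: 0 + (−0.5)(−0.4) = 0.20
- half: 0.10 + (−0.5)(−0.2) = 0.20
- none: 0.20 + (−0.5)(0) = 0.20

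| Mediation through M | Missing | Available cases, M omitted | Plan's rule, M as covariate | M used only to impute, by arm |
|---|---|---|---|---|
| Full | 21.6% | 0.177 | −0.001 | 0.200 |
| Half | 23.0% | 0.185 | 0.097 | 0.198 |
| None | 24.4% | 0.200 | 0.199 | 0.200 |

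The last row behaves as any pre-randomization variable would, and there the rule is sound. In the first two rows the rule does worse than making no correction. The last column used a single regression imputation by arm, so it supports the point estimate and not the standard error. The single follow-up does not reproduce the joint baseline and follow-up model, so the sizes are illustrative.

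**Multiple imputation.** A likelihood-based mixed model and multiple imputation draw on the same information when they use the same variables. Here imputation can use M while the treatment model omits it. In the full-mediation row that moves the estimate from 0.177 to the true 0.200, so imputation does recover something.

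**Scale on EQ5D.** At the plan's hypothesized 17% and 11%, the part of the effect that runs through complications is 0.06 times the EQ5D loss per complication. For assumed losses of 0.15 and 0.25 this is 0.06 × 0.15 = 0.009 and 0.06 × 0.25 = 0.015.

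**The case against.** The plan never says that post-randomization variables will be adjusted for, and the only timing it names is pre-operative. A reader might infer that such adjustment is planned; the text shows only that it is permitted. Missing predictor data also describes all other potential predictors as preoperative measurements of the longitudinal outcomes, which suggests that baseline covariates were in mind. For those the rule works.

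This does not close the gap. The preoperative EQ5D values are already in the joint model and the minimization factors are already adjusted for, so a rule to find further predictors must reach other variables. Under Pre-specified ancillary analyses the plan does exclude variables lying on the causal pathway, but only for those observational models.

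Two further objections stand. First, the reach is narrow: two secondary outcomes, and only if missingness exceeds 20%, missing at random is accepted and a variable affected by allocation is chosen. Second, the sentence on multiple imputation is defensible when both models use the same variables, so it needs a qualifier and need not be deleted.

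**Conclusion.** The concern holds as a gap in the rule. For any variable that allocation affects, the statement of unbiasedness is wrong for the total effect by b·m, the mediated part. In the illustration that is all of a 0.20 SD effect under full mediation, about half under half mediation, and nothing when allocation does not affect the variable. These sizes rest on assumed slopes, missingness and degree of mediation.

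Two stronger readings are tempting, and the documents do not support them:

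- *The bias is towards no difference.* That requires the direct effect to be zero or to share the sign of the mediated effect. With d = −0.009 and a mediated part of +0.009, the total is 0 and the adjusted estimate is −0.009, away from the null. The plan gives no direct effect.
- *A clear EQ5D difference would be reported as zero.* Near-total loss restates an assumption of full mediation. At the plan's own event rates and an assumed loss of 0.15, the mediated part is only 0.009.

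The primary outcome is untouched. The point merits a change of wording because it is cheap and the plan's present claim is unconditional.

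**What to change.** 1. Limit covariates added to the EQ5D mixed model to variables measured before randomization. Randomization follows surgery in this trial, so intra-operative details and pre-randomization transfusions remain available; the boundary that matters is randomization, not the operation.
2. If post-randomization variables predict missingness, use them only as auxiliary variables in multiple imputation carried out by arm. Then fit the planned mixed model without them and combine the results with Rubin's rules, which Table 4 already provides for other outcomes.
3. State that the unbiasedness claim applies to covariates allocation cannot affect, and that multiple imputation adds nothing only when the imputation and analysis models use the same variables.

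The cost is a few lines of text and one extra analysis, needed only above 20% missingness when post-randomization variables predict it. The Discussion says the plan has already been executed, so the practical step may be to report whether the rule was triggered for EQ5D and, if so, which variables entered the model.
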